**Fig. 1 Fig1:**
[figure not shown]
A flowchart of the study design

A Consolidated Standards of Reporting Trials (CONSORT) checklist for this study is provided in Additional file 2. The Standard Protocol Items: Recommendations for Interventional Trials (SPIRIT) checklist is provided in Additional file 3.

### Randomization

Patients who will receive curative radical resection for hilar cholangiocarcinoma would be randomly assigned (1:1) to regional lymphadenectomy or extended lymphadenectomy by computer-generated allocation based on the envelope method and the hierarchical block randomization method. The envelopes are sealed, opaque, and sequentially numbered. Randomization is performed by the trial coordinator (Study Group of Biliary Surgery of the Surgery Branch of the Chinese Medical Association). The random number table and the block assignment number table will be kept confidential by the full-time secretary of this project. Center-stratified block-permuted randomization is used in this trial. Trial participants are subdivided into strata such as centers; then permuted block randomization is used for each stratum with a block size of 4.

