### Blinding

Concerning random allocation, a sealed envelope will be issued to the surgeon before the operation by a project secretary. Normally there are two secretaries who are recruited for the clinical trial data management who are not involved in the operation. Then the surgeon unpacks the envelope and performs the operation according to the allocation in the envelope. The patients, outcome assessors, pathologists, and data analysts will not know the grouping information.

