### Statistical analysis

Concerning the primary endpoint (overall survival), the log-rank test for univariable testing and Cox regression would be used to compare the long-term prognosis among patients in the extended lymphadenectomy group and the regional lymphadenectomy group in the intention-to-treat population. Secondary endpoints include DFS, survival without recurrence of regional nodal metastases, distant metastasis-free survival, the primary complication within 30 days after surgery (Clavien-Dindo grade > II), and perioperative mortality. Time zero is set as the time of randomization. After enrollment, all patients who have been randomized would be included in the full analysis set (FAS). On the basis of the FAS, patients who meet the inclusion and exclusion criteria (Table 1), are compliant, and do not violate the clinical trial protocol would form the per protocol set (PPS).

**Table 1 Tab1:** Eligibility criteria in Relay-HC trial

Inclusion criteria	
1. Age > 18 years old and ≤ 80 years old	
2. Diagnosis of hilar cholangiocarcinoma by preoperative imaging and laboratory examination; confirmed as biliary malignant tumor by intraoperative frozen and postoperative pathology; evaluated as resectable by preoperative imaging	
3. Preoperative CT/MRI shows no obvious lymph node metastasis of groups 9, 14 and 16	
4. Child-Turcotte-Pugh A–B grade of liver function	
5. Residual liver volume > 30% 6. ASA grade 1–3	
7. The patient has self-care ability, understands and voluntarily signs the written informed consent, and is able to complete the follow-up plan	
8. Female patients of gestational age must be excluded from pregnancy	
9. The patient has signed the written informed consent form before the screening test	
Exclusion criteria	
1. Tumor R1 resection	
2. The patient has obvious heart, lung, brain, or kidney dysfunction that affects the treatment of cholangiocarcinoma	
3. The patient has a history of other malignancies	
4. Child-Turcotte-Pugh C grade of liver function	
5. ASA grade 4–6	
6. Females who are pregnant or breastfeeding	
7. Patients who are not suitable for the study as determined by the researcher	

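### A published, fixed block size of 4 within each center lets a team that tracks its allocations deduce up to one third of assignments before entry

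*Protocol article*

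**What the plan says.** The Randomization section of the protocol article describes a 1:1 computer-generated allocation delivered in envelopes. On stratification it says "Center-stratified block-permuted randomization is used in this trial", and on blocks "then permuted block randomization is used for each stratum with a block size of 4". Center is the only stratum named, though the wording introduces it as an example. Two safeguards are stated: "The envelopes are sealed, opaque, and sequentially numbered", and "The random number table and the block assignment number table will be kept confidential by the full-time secretary of this project".

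The Blinding section says that a secretary who takes no part in the operation issues the envelope to the surgeon beforehand. "Then the surgeon unpacks the envelope and performs the operation according to the allocation in the envelope". The blinded parties are then listed: "The patients, outcome assessors, pathologists, and data analysts will not know the grouping information". Surgeons are not on that list and could not be.

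Two parts of eligibility depend on judgement at the center. The Case selection section asks for an anticipated complete resection, assessed by the center's multidisciplinary team. Exclusion criterion 7 in Table 1 reads "Patients who are not suitable for the study as determined by the researcher".

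**The concern.** Opaque envelopes and a confidential list protect the list itself. They do not prevent deduction from allocations already seen when every block has the same known length. In a block of 4 with two places per arm, the fourth assignment is fixed once three are known, and the last two are fixed once the first two fall in the same arm.

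The people who learn the allocations, the surgeons, belong to the teams that judge resectability and suitability. If someone who influences entry knows or can guess the next arm, that knowledge can affect whether a particular patient is entered. The arms could then differ in prognosis or fitness at baseline, which would distort both the overall survival comparison and the complication comparison. Blinding patients, assessors, pathologists and analysts does not address this, because the selection happens before randomization. Intention-to-treat analysis does not correct it either, for the same reason.

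**Working it through.** **Inputs from the protocol article.** Allocation 1:1, block size 4 and stratification by center (Randomization); 734 patients and 15 centers (Abstract). The article gives no predictability figure, so there is none to reproduce.

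**Assumptions.** The person guessing knows the block size, has seen all earlier allocations at the center, and knows where blocks begin. Center is the only stratum.

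**Assignments known with certainty.** A block of 4 has 6 equally likely sequences: AABB, BBAA, ABAB, ABBA, BABA, BAAB.
- In AABB and BBAA the last two assignments are determined.
- In the other four only the last one is.
- Expected number per block = (2×2 + 4×1)/6 = 8/6 = 1.33, and 1.33/4 = 33.3%.
- Over the trial: 734/3 = 244.7, about 245 assignments.

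**Incomplete last blocks.** An average center enters 734/15 = 48.9, about 49 patients, which is 12 full blocks and one patient over. Certain assignments = 12×1.33 = 16, and 16/49 = 32.7%. A simulation with 49 patients per center gave 32.6%. The conclusion does not change.

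**Best guess.** Always guess the arm with more places left in the block.
- First position: 1/2.
- Second: 2/3.
- Third: 1/3×1 + 2/3×1/2 = 2/3.
- Fourth: 1.
- Average = (0.5 + 0.667 + 0.667 + 1)/4 = 70.8%, against 50% under simple randomization.

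**Alternatives.** For a fixed block of size 2m the expected share known with certainty is 1/(m+1). The random-order rows were simulated with 49 patients per center and a guesser who knows the set of sizes but not their order.

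| Scheme | Known with certainty | Best guess correct |
|---|---|---|
| Fixed 4 (as planned) | 33.3% | 70.8% |
| Fixed 6 | 25% | 68.3% |
| Fixed 8 | 20% | 66.6% |
| Random order of 4 and 6 | about 5.5% | about 69% |
| Random order of 4, 6 and 8 | about 2.4% | about 68% |

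Varying the block size nearly removes certainty (33.3% to about 2.4%). It does little for guessing: 70.8% to about 68%, some 3 percentage points.

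**The case against.** A reader might infer that surgeons see every allocation and that one third of assignments are in fact known. The article does not say so. Each surgeon opens the envelope for the operation at hand, and the Procedure section speaks of surgeons in the plural at each center, so the full figure is reached only where the team shares and records its allocations. The wording on strata also leaves room for further strata, which would make tracking harder. This objection stands, and it makes one third an upper figure that depends on tracking.

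A reader might also call the trial open-label. That does not fit the Blinding section, which keeps patients, outcome assessors, pathologists and data analysts unaware of the arm. Only the surgeons' knowledge matters here.

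There are practical brakes. All patients go through multidisciplinary evaluation, Table 1 requires consent before the screening test, and a secretary outside the operation releases the envelope. Planned recruitment runs for 60 months (Trial status), so accrual averages 734/15/60, about 0.8 patients per center per month, which leaves little queue to reorder. Declining a patient under the discretionary exclusion remains possible. These points lower the likelihood of steering without removing the means.

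It would be too strong to say that such bias is beyond repair in the analysis. The planned Cox regression could adjust for measured baseline factors, but selection on unmeasured ones would remain. Nor is it a fault that the article describes no irrevocable registration before the envelope is released. That is operational detail which an article may leave to the full protocol.

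Finally, small fixed blocks have a purpose: they keep the arms balanced within 15 centers with differing case quotas. That is a fair reason for blocking, but it does not require a single published size.

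**Conclusion.** The concern holds as an avoidable risk. The stated rule lets a team that tracks its center's allocations deduce up to about one third of assignments before entry (about 245 of 734) and guess correctly about 71% of the time. The stated concealment measures do not prevent this, and eligibility leaves room for judgement.

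The arithmetic is exact under its assumptions: known block size, shared knowledge of past allocations, known block boundaries and no stratum other than center. Where these fail, the deducible share is smaller. The article gives no basis for saying that steering took place or for putting a size on any bias in survival or complications. Because the remedy is simple and its gain is mainly in certainty, the point is graded as a cheap improvement.

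**What to change.** Generate the envelopes not yet issued from a new list with block sizes in random order within center, for example 4, 6 and 8, and withhold both the sizes and their order from the sites. Recruitment was planned from 30 July 2018 to 30 July 2023, so the change can apply only to envelopes still unissued.

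The cost is one new computer-generated list. The largest possible imbalance within a center rises from 2 to 4. In the extreme case where all 15 centers stop mid-block in the same direction, the overall imbalance could reach 15×4 = 60 instead of 15×2 = 30 of 734. No endpoint, sample size or treatment changes. The sponsor should not expect the change to end guessing, since best-guess accuracy stays near 68%.

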### Procedure

The routine approach for hilar cholangiocarcinoma surgery is based on the National Comprehensive Cancer Network (NCCN) Guidelines Insights: Version 2.2019 Hepatobiliary Cancers [13]. The surgical procedures consist of (extended) hemi-hepatectomy and complete lymphadenectomy of the hepatoduodenal ligament. The (extended) hemi-hepatectomy contains en bloc excision of the liver hilum, extrahepatic bile ducts, and caudate lobe. Portal vein excision and reconstruction would be performed when the tumor infiltrates into the portal vein bifurcation. In this study, we will utilize the lymph node classification system by the Liver Cancer Study Group of Japan (Additional file 1: Figure S1) [14]. Patients in the regional lymph node dissection group will receive radical resection and numbers 8a/p, 12a/b/c/h/p, 13a lymph nodes dissection. In contrast, patients in the extended lymph node dissection group will receive radical resection and numbers 8a/p, 9, 12a/b/c/h/p, 13a, 14, 16 lymph nodes dissection. Experienced surgeons in each center will be educated in a standardized surgical approach, especially the surgical procedures and lymph node harvest procedures. There will be digital recording (video and photography) for each operation, which will be evaluated by third-party surgical experts, namely the data monitoring committee (DMC). The intraoperative evaluation, safety assessment, and tumor specimens will be evaluated by the surgical teams who perform the surgery as well as pathologists.

### Blinding

Concerning random allocation, a sealed envelope will be issued to the surgeon before the operation by a project secretary. Normally there are two secretaries who are recruited for the clinical trial data management who are not involved in the operation. Then the surgeon unpacks the envelope and performs the operation according to the allocation in the envelope. The patients, outcome assessors, pathologists, and data analysts will not know the grouping information.

### Follow-up

To improve data quality, double data entry would be performed by the two secretaries. Final study follow-up is scheduled at 30 days after surgery, including perioperative mortality and operative complication evaluation. Long-term follow-up assessments including tumor markers, chest radiographs, upper abdomen enhanced CT, and survival status are scheduled at 6 months, 1 year, 3 years, and 5 years after surgery.

### Observation indices

The primary endpoint will be the 5-year OS rate. The secondary efficacy index includes the primary complication (Clavien-Dindo grades > II) within 30 days postoperatively, perioperative mortality, 6-month OS and DFS, 1-year OS and DFS, 3-year OS and DFS, and 5-year DFS. Cancer-specific survival is determined at the time of cholangiocarcinoma-related death. Disease-free survival is the time to any recurrence. The efficacy evaluation is based on the postoperative pathology: if the postoperative pathological margin is negative and LN ≥ 6, the operation is considered to have achieved the desired purpose. The safety index includes vital signs, adverse events, and clinical laboratory parameters (blood routine, urine routine, myocardial enzymes, coagulation, blood biochemistry, electrocardiogram, cardiac ultrasound), as well as early withdrawal (Fig. 2).

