## Methods

### Design

The Relay-HC trial is a prospective, multicenter, randomized controlled trial. Patients who will receive curative radical resection for hilar cholangiocarcinoma would be randomly assigned (1:1) to receive either regional lymphadenectomy or extended lymphadenectomy. The sample size calculation resulted in a requirement of 734 patients. On the basis of previous data, the median 5-year OS of patients with hilar cholangiocarcinoma who underwent regional lymphadenectomy (P1) was 0.17 (0.07–0.20) [6–9], and the 5-year OS for those with extended lymphadenectomy (P2) was 0.26 [3, 10, 11]. The α level (type I error) is set as 0.05 (one-sided), β is set as 0.2, and the power is set as 0.8. The formula to calculate the sample quantity for a high-quality clinical trial is [12]:
$$ {n}_1={n}_2=\frac{\Big[{u}_a\sqrt{2p\left(1-p\right)}+{u}_{\beta}\sqrt{p_1\left(1-{p}_1\right)+{p}_2\left(1-{p}_2\right)\Big]{}^2}}{{\left({p}_1-{p}_2\right)}^2} $$

The minimum sample size for each group is 330. As the actual sample size includes 10% shedding, the actual sample size of each group is thus 367 patients.

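### Disease-free survival is defined by recurrence alone, so deaths without documented recurrence are never DFS events and the DFS rates are overstated

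*Protocol article*

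**What the plan says.** The protocol article, section Observation indices, names as secondary endpoints "6-month OS and DFS, 1-year OS and DFS, 3-year OS and DFS, and 5-year DFS" and gives one definition: "Disease-free survival is the time to any recurrence". The sentence before it places cholangiocarcinoma-related death in a different quantity, cancer-specific survival.

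The Statistical analysis section lists the endpoint again ("Secondary endpoints include DFS, survival without recurrence of regional nodal metastases, distant metastasis-free survival") and fixes the origin ("Time zero is set as the time of randomization"). It neither redefines the DFS event nor says what happens to a patient who dies without recurrence. The abbreviation list only spells out the term.

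The Follow-up section gives the long-term schedule: tumor markers, chest radiographs, enhanced CT and "survival status are scheduled at 6 months, 1 year, 3 years, and 5 years after surgery". The intervals from 1 to 3 years and from 3 to 5 years are therefore two years each. The article does not mention recurrences found between these visits.

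**The concern.** Disease-free survival should fail at recurrence or death. With recurrence as the only event, the quantity is time to recurrence under another name, and a patient who dies soon after the operation never fails on it.

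This matters here because the trial asks whether a larger operation improves prognosis without more harm, and the Discussion names added morbidity as a main worry about extended dissection. A DFS comparison that ignores death cannot weigh fewer recurrences against more deaths.

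The visit schedule can enlarge the effect. With planned 5-year OS of 17% and 26%, some patients may relapse and die inside a two-year gap. If no recurrence is documented in that time, neither the relapse nor the death enters DFS.

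**Working it through.** **No figure to reproduce.** The article states no DFS rate, event count or power. Its only usable inputs are the 5-year OS rates in the Design section, 0.17 (regional) and 0.26 (extended), and the visit times in the Follow-up section.

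**Step 1: deaths inside the two-year gaps.** Assume exponential survival, S(t) = exp(-λt) with λ = -ln(S(5))/5.

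| 5-year OS | λ | S(1) | S(3) | Die in years 1-3 | Die in years 3-5 | Share of 5-year deaths |
|---|---|---|---|---|---|---|
| 0.17 | 0.354 | 0.702 | 0.345 | 35.6% | 17.5% | 53.2/83 = 64% |
| 0.26 | 0.269 | 0.764 | 0.446 | 31.8% | 18.6% | 50.4/74 = 68% |

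This is context only. It counts every death in the gaps, including patients whose recurrence was already documented at 6 months or 1 year.

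**Step 2: a model for the size.** The following assumptions are not in the article:
- The first event (recurrence, or death without recurrence) has constant hazard h.
- A fraction f of first events are deaths without recurrence: 5%, 10% or 20%.
- Survival after recurrence is exponential with median 0.5, 1 or 1.5 years (hazard μ = ln 2/median).
- Visits are counted from time zero.
- Patients who die without documented recurrence are censored at death.

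Then OS(t) = exp(-ht) + (1-f)·[h/(μ-h)]·[exp(-ht) - exp(-μt)], and h is chosen so that OS(5) equals 0.17 or 0.26. DFS counting recurrence or death is exp(-ht).

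**Step 3: middle case** (OS 0.17, f = 0.10, median 1 year, so μ = 0.693). Calibration gives h = 0.567.
- DFS with death as an event: exp(-3h) = 18.3% at 3 years and exp(-5h) = 5.9% at 5 years.
- Definition as written, every recurrence found at once: exp(-0.9·3h) = 21.7% at 3 years, about 3 points too high.
- Definition as written, recurrence found only at visits: over an interval of length d, the chance of being recurrence-free given alive is A/(A+B), with A = exp(-hd) and B = 0.9·[h/(μ-h)]·[exp(-hd) - exp(-μd)]. For d = 0.5 this is 0.753/(0.753+0.186) = 0.802. For d = 2 it is 0.322/(0.322+0.290) = 0.526. The 3-year value is 0.802² × 0.526 = 33.8%, about 16 points too high. The 5-year value is 0.338 × 0.526 = 17.8%.

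That 17.8% exceeds the 17% OS used to build the case, which a true DFS cannot do.

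**Step 4: full range** over all values of f and median, at both OS rates.

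| Detection of recurrence | 5-year deaths with no documented recurrence | Overstatement of 3-year DFS |
|---|---|---|
| All found when they occur | 5-25% | 1-8 points |
| Half found between visits | 19-45% | 3-20 points |
| Only at scheduled visits | 32-69% | 4-32 points |

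The bias is upward in every case.

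**The case against.** **Handling of deaths may be set elsewhere.** The article does not say that deaths are censored, and such rules commonly sit in a full protocol or analysis plan that is not shown. That is fair as to the censoring rule. The event, however, is defined in a complete sentence, and it leaves death out. The direction also does not depend on censoring. If deaths were treated as competing events, the 3-year recurrence-free proportion in the middle case with full detection would be 1 - 0.9 × (1 - 0.183) = 26.4%, still above 18.3%.

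**Size.** A reader might infer from the visit gaps that a large share of failures is lost. That holds if recurrences are recorded only at scheduled visits. The article schedules assessments but does not say that recurrences found in between go unrecorded, and its definition covers any recurrence. With full detection the overstatement falls to 1-8 points.

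**Direction between arms.** A reader might also infer that the arm with more surgical deaths would look better on DFS. This does not follow in general. If early deaths are unrelated to recurrence risk, censoring them leaves the expected recurrence curve unchanged: the arm is not penalised, but it gains nothing. It gains only if those who die early were also likelier to recur, and the article gives no evidence on that. Nor are patients censored at death counted as disease-free afterwards; they leave the risk set.

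**Safety is measured elsewhere.** Perioperative mortality is its own secondary endpoint and OS counts every death. This stands, and it limits the consequence to the DFS results.

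**Conclusion.** The definition is wrong as written. Death is not a DFS event anywhere in the article, so the four DFS endpoints are time to recurrence and overstate disease-free survival. The direction follows from the definition. The size depends on assumed detection, the assumed share of deaths without recurrence and assumed survival after recurrence: across the cases examined, 1 to 32 percentage points at 3 years, with only the lower part (1-8) applying if recurrences are always found promptly.

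The DFS comparison cannot show a mortality difference between the arms; a bias towards one arm is possible but not established. Primary OS and the sample size do not use DFS and are unaffected.

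**What to change.** In Observation indices, define DFS as the time from randomization (the time zero already set in Statistical analysis) to first recurrence or death from any cause, whichever comes first. If time to recurrence is also wanted, report it under that name, with death as a competing event.

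It would help to state how a recurrence found between scheduled visits is dated. An interval-censored analysis of the two-year gaps is optional and is not needed to correct the definition.

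The cost is a change of wording. Deaths are already collected for OS, so no new data are required. DFS estimates will be lower by the amount now overstated.

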**Fig. 2 Fig2:**
[figure not shown]
Enrollment, intervention, and assessments in the Relay-HC trial

Specifically, the intraoperative evaluation includes the length of the operation, intraoperative hemorrhage, intraoperative blood transfusion, time of hepatic occlusion, vascular anastomosis, the area and number of lymph nodes dissected, and so on.

Concerning the tumor-related evaluation, tumor specimens will be sent for pathological evaluation about the quality of the specimens, grading, pathological stage, tumor embolus in vein, perineuronal invasion, lymph node collection, and the ratio of positive lymph nodes.

Concerning feasibility and safety, routine blood examination, hepatic and renal function, and the biochemical test will be performed the day after the surgery and then every 3 days. Chest and upper and lower abdomen CT will be performed on the seventh postoperative day to evaluate pleural effusion, lung infection, ascites, and abdominal infection. Additionally, vital signs and drainage will be monitored.

